### Allocation and sequence generation

Patients satisfying the inclusion criteria and willing to enter the study are randomized to one of the two study arms after signing the informed consent. The randomization is performed in a 1:1 fashion. The allocation to immediate or early UC removal group is achieved by creating a randomization list. The randomization list has been obtained by an online program available at https://www.sealedenvelope.com/simple-randomiser/v1/lists. A common list is created for all participating centers and patients’ allocation communicated by a member of the proposing center to a member of other centers the morning of surgery. The operating surgeon will be blinded to allocation of the patients until the end of surgery.

### Data collection and management

Trained members from each surgical staff oversee the data collection and recording. Baseline demographic data, as well as preoperative, intraoperative, and postoperative variables, are collected using a specifically created datasheet and stored in a specifically created dataset. The same datasheet and dataset are used in all centers. Data on patients’ comorbidities were registered with particular interest to previous prostatic surgery, history of prostatic disease, or medical therapy for benign prostatic hyperplasia.

To reduce as much as possible the variability among patients in reporting symptoms and pain intensity, the patient is instructed on symptoms and NRS scale by the same member of the surgical staff at the time of accrual (15–20 days before surgery) and the day before surgery. To reduce the variability related to data collection, the same member will collect all other investigated variables.

### Statistical analysis

Statistical analyses will be performed on an intention-to-treat (ITT) basis using IBM® SPSS® Statistics software version 21.0 (IBM Corporation, Armonk, NY).

An intention-to-treat analysis (ITT) will be used on all randomized subjects and, where appropriate, an imputation method will be established. It will be also performed per-protocol (PP) analysis that will include all subjects who have finished the catheter removal without major deviations from the research protocol. In non-inferiority studies, both ITT and PP analyses are recommended and should support non-inferiority.

The primary endpoint is AUR. Non-inferiority in the main outcome of the immediate UC removal group compared to 24-h UC removal will be evaluated by test for proportions. The non-inferiority of the immediate UC removal group will be accepted if the upper limit of the 95% confidence interval of the difference in proportions is greater than the non-inferiority threshold value of 6%.

The secondary objectives are assessing the benefits in choosing one procedure or the other, immediate UC removal versus 24-h UC removal. Descriptive statistics and plots will be used to compare the two groups taking into account: (1) UTI rate; (2) overall rate of re-catheterization; (3) pain intensity at 6, 12, 24, 48, and 72 h after surgery; (4) time from surgery to resumption of first oral intake (liquid and soft diet), bowel movements (flatus and defecation), mobilization to chair, and walking; (5) rate of overall, general, and surgery-related post-operative complications; (6) length of hospital stay.

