### Outcome measures

#### Primary endpoint

To demonstrate the non-inferiority of immediate compared to early (within 24 h from the completion of surgery) removal of UC in patients undergoing MICR in terms of AUR. AUR is defined as the inability to urinate within 8 h after UC removal or difficulty of voiding with a postvoid residual volume (PVR) measured by ultrasound greater than 300mL.

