### Sample size calculation

The null hypothesis is that the immediate UC removal is significantly inferior to the 24-h UC removal. Based on the current literature, in order to test the alternative hypothesis of non-inferiority of immediate UC removal vs. 24-h UC removal, the sample size is calculated using the incidence of AUR. Available data show that the AUR rate can be estimated as high as 3% after MICR [14–16].

Sample size was calculated based on the following data. Considering an expected AUR rate of 3% (p1) for the 24-h UC removal group, we choose the non-inferiority limit of δ = 6% with δ = p2-p1, considering acceptable a p2 of 9% for the immediate UC removal group. We calculated that 200 patients are required in each group to give 80% power at a 5% significance level. Considering 8% dropout, the total number of patients to be enrolled is 216, 108 per group (Non-Inferiority Tests for the Difference Between Two Proportions, PASS 14)

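### The primary decision rule is reversed: non-inferiority is accepted when the upper confidence limit lies above the 6% margin, not below it

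*Protocol article*

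**What the plan says.** The Primary endpoint section makes AUR the outcome, and it is a harm: "AUR is defined as the inability to urinate within 8 h after UC removal", or difficult voiding with a residual volume above 300 mL. Fewer events are better.

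The Sample size calculation section fixes the direction and the margin. The control rate comes first: "Considering an expected AUR rate of 3% (p1) for the 24-h UC removal group". The margin follows: "we choose the non-inferiority limit of δ = 6% with δ = p2-p1", and then "considering acceptable a p2 of 9% for the immediate UC removal group". So p2 − p1 is immediate minus 24-h, and a positive value means more retention with immediate removal. The same section gives the null: "The null hypothesis is that the immediate UC removal is significantly inferior to the 24-h UC removal".

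The Statistical analysis section then gives the decision rule. Non-inferiority is accepted if the "upper limit of the 95% confidence interval of the difference in proportions is greater than the non-inferiority threshold value of 6" per cent. That sentence does not restate which group is subtracted from which. No other part of the article gives a numerical acceptance rule.

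**The concern.** For a harm, with the difference taken as experimental minus control, the upper confidence limit is the largest excess of harm still compatible with the data. Non-inferiority is shown when that limit stays below the margin. The article asks for it to exceed the margin. Read literally, a trial succeeds when the data cannot exclude an excess above 6 points, and fails when they can.

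This is the success criterion for the primary endpoint. A pre-specified rule exists so that the analyst is bound by it and readers can check the result against it. With the rule as published, a favourable result breaches the stated criterion and a harmful one meets it. The investigators would have to follow a wrong rule or depart from the published one after seeing the data.

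**Working it through.** **Inputs.** From the Sample size calculation section: 24-h rate p1 = 3%, margin δ = 6 points on p2 − p1, 80% power, 5% significance, 8% dropout, 216 patients in total (108 per group). From the Statistical analysis section: 95% confidence interval, accept if the upper limit exceeds 6%. Assumptions: the interval is a two-sided Wald interval, and 100 patients per group are evaluable.

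**Why 100 per group.** The article's total can be reproduced with equal true rates of 3%, unpooled variance and one-sided alpha 0.05:

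n = (z₀.₉₅ + z₀.₈₀)² × [p1(1 − p1) + p2(1 − p2)] / δ² = (1.645 + 0.842)² × (2 × 0.03 × 0.97) / 0.06² = 99.95, so 100 per group.

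Then 100 × 1.08 = 108 per group, 216 in total, as stated. The section also says 200 are needed in each group, which does not fit 216 in total. Results for 108 and 200 per group are therefore shown as well.

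**Single results, 100 per group.** Upper limit U = d + 1.96 × √[p2(1 − p2)/100 + p1(1 − p1)/100], with d = p2 − p1 (observed rates):

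| Events, immediate vs 24-h | Calculation | U | As written | Correct rule |
|---|---|---|---|---|
| 1 vs 3 | −0.02 + 1.96 × 0.01975 | 1.9% | fails | passes |
| 3 vs 3 | 0 + 1.96 × 0.02413 | 4.7% | fails | passes |
| 9 vs 3 | 0.06 + 1.96 × 0.03332 | 12.5% | passes | fails |
| 12 vs 3 | 0.09 + 1.96 × 0.03670 | 16.2% | passes | fails |
| 15 vs 3 | 0.12 + 1.96 × 0.03969 | 19.8% | passes | fails |

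**Probability of declaring non-inferiority under the rule as written.** These come from summing the exact binomial probabilities over all pairs of event counts with U > 6%, with the true 24-h rate at 3%:

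| True immediate rate | 100 per group | 108 per group | 200 per group |
|---|---|---|---|
| 0% | 0.000 | 0.000 | 0.000 |
| 3% | 0.294 | 0.262 | 0.067 |
| 5% | 0.666 | 0.643 | 0.451 |
| 9% (margin) | 0.965 | 0.964 | 0.967 |
| 15% | 1.000 | 1.000 | 1.000 |

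With a Newcombe interval and 100 per group, the values are 0.452 at 3% and 0.977 at 9%.

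**Rule with the inequality corrected (U < 6%), 100 per group, Wald.** Acceptance has probability 0.706 at 3%, 0.035 at 9% and practically 0 at 15%.

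**Does reversing the subtraction rescue the sentence?** No. With 24-h minus immediate, non-inferiority would require the *lower* limit to be above −6%. An upper limit above +6% would still reject 3 vs 3 events (U = 4.7%). It would also reject 1 immediate vs 3 at 24 h, where U = 0.02 + 1.96 × 0.01975 = 5.9%.

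**The case against.** The strongest reply is that this is a slip of one word and the intended direction is recoverable. The null hypothesis, the definition of δ and the repeated statement of a non-inferiority aim all point the same way, and a competent analyst would apply *less than*. The direction of subtraction, absent from the Statistical analysis section, can be read from the Sample size calculation section. All of this is fair, and the error is most likely typographical. It does not make the sentence right. The sentence is the only acceptance rule in the article, and a reader has to overrule it to reach the intended test. A statistical analysis plan, if one exists, may have it right, but the published statement would still need correcting.

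A second reply is that the 29% figure at equal rates depends on the assumed group size. That stands: it falls to 26% at 108 per group and 7% at 200. The error at the margin does not depend on it and is 96–97% throughout.

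A third reply is that specifying a two-sided 95% interval has a cost in power. The article's total reproduces only at one-sided 5%. A two-sided 95% interval at equal 3% rates gives power of about 0.71 with 100 per group and 0.74 with 108, against the planned 80%. This is true, but a two-sided interval is the ordinary reading of the 95% interval already in the text. The mismatch between interval and sample size therefore exists already and is a separate question from the reversed inequality.

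**Conclusion.** The concern holds. The decision rule contradicts the article's own margin, direction and null hypothesis, and no reading of the sentence turns it into a non-inferiority test. Applied literally, the chance of declaring non-inferiority when the true excess equals the margin is about 96.5%, against a stated significance level of 5%. With the inequality corrected it is about 3.5%. These figures assume a 24-h rate of 3%, 100 evaluable patients per group and a two-sided 95% Wald interval. The figure at the margin is almost the same at 108 and 200 per group and with a Newcombe interval. The finding that the direction is wrong needs none of these assumptions. It must be corrected, preferably before the primary outcome is analysed.

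**What to change.** In the Statistical analysis section, replace the acceptance sentence with, for example: *Non-inferiority will be accepted if the upper limit of the two-sided 95% confidence interval for the AUR rate with immediate removal minus the AUR rate with 24-h removal is less than 6 percentage points, in both the ITT and the PP analysis.* The ITT and PP clause only makes explicit what that section already asks for.

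In the Sample size calculation section, state the hypotheses in terms of the margin: H0: p2 − p1 ≥ 6%; H1: p2 − p1 < 6%.

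The cost is these wording changes and a published correction. Reversing the inequality alters neither recruitment nor conduct, and it leaves the sample size as it is. Whether the sample size matches a two-sided 95% interval should be settled separately.

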### Auditing trial conduct plan

There are no plans for trial audit given the short duration of the trial intervention and follow-up.

### Dissemination plans

The results of the trial will be published in peer-reviewed academic journals and presented at national and international scientific meetings. Additionally, a lay summary containing the study aim, salient findings, conclusions, and a take home message will be prepared and distributed through electronic media including newsletters, social media, and websites.

## Discussion

UC is routinely adopted after major surgery for preventing AUR and facilitating fluid balance monitoring. Nonetheless, the presence of a UC is associated with reduced mobility and increased patients’ discomfort [1]. Additionally, after colorectal surgery, urinary catheter placement could be complicated by a UTI rate of almost 4%, which represents the highest rate among gastrointestinal surgical procedures [6, 17]. Although recommended by ERAS guidelines [2], early UC removal is one of the most problematic items to be achieved. In a recent paper, the PeriOperative Italian Society (POIS) showed a rate of UC removal within 24 h from surgery of 72.5% among patients undergoing an elective colorectal resection within an ERAS program [3]. Nonetheless, compliance to this item has been shown to increase up to 96% when specific protocols are implemented [14].

Early UC removal together with early withdrawal of IV fluids have been reported to be crucial for reducing overall morbidity and shortening LOS [3]. In fact, it is well demonstrated that IV fluid over prescription is associated with cardiopulmonary overload and intestinal and anastomotic edema [18, 19].

Although feasibility and advantages of early UC removal following colorectal surgery have been demonstrated, the time extent of UC to be in place remains debated [11–13, 20]. Current evidence is based on retrospective, unpowered and unbalanced cohort studies. Mixing colon and rectal surgery, open and minimally invasive approach, epidural as well as strong opioid-based analgesia regimens are among the most common bias making a definitive statement difficult to be made.

In this randomized controlled trial, we will focus on MICRs not requiring pelvic dissection. This will allow us to analyze a homogeneous cohort of patients in terms of the extent of surgery and pain management protocols. Epidural anesthesia is no longer suggested by ERAS guidelines in laparoscopic surgery and, being a well-known risk factor for AUR, it has been considered an exclusion criterion [2]. This together with the fact that, at participating centers, open surgery is mostly reserved to urgent or very advanced cases helps the results to be focused on patients undergoing MICRs specifically.

Even though completely avoiding UC placement could be considered an option [12, 20], evidence about this approach is currently even poorer from the literature. In addition, the frequent use of suprapubic incision for specimen extraction, both in left- and right-sided colonic resections, lead us to prefer the current study approach.

In conclusion, this study comparing immediate versus early (within 24 h from surgery) UC removal represents a solid option to demonstrate the possibility of moving a step forward in reducing the stress and discomfort for our patients undergoing elective minimally invasive colonic surgery.

### Trial status

Recruitment has started on February 15, 2022, and it will be completed within the end of June 2023 (UniVR Prog. 3589CESC).

## Data Availability

The datasets used and/or analyzed during the current study are available from the corresponding author (CP) on reasonable request.

## Abbreviations

AUR: Acute urinary retention
ERAS: Enhanced Recovery After Surgery
ICU: Intensive care unit
IQR: Interquartile range
ITT: Intention-to-treat
IV: Intravenous
LOS: Length of stay
MICR: Minimally invasive colonic resection
NOSES: Natural orifice specimen extraction surgery
NRS: Numerical rating scale
POD: Post-operative day
PP: Per-protocol
PVR: Postvoid residual volume
TAP: Transversus abdominis plane
UC: Urinary catheter
UTI: Urinary tract infection
